**Fig. 3 Fig3:**
[figure not shown]
Grouping of the retrieved lymph nodes

**Fig. 4 Fig4:**
[figure not shown]
(**a**) Anterior and (**b**) posterior photographs of a fresh laparoscopic modified complete mesocolic excision specimen taken with a metric scale. The caecal tumour and ileocolic vascular tie are indicated by forceps. Note the smooth posterior surgical margin and intact peritoneal window

### Level of central radicality

The level of central radicality will be determined by participating surgeons based on the preoperative and intraoperative findings regarding the depth of tumour invasion and the status of lymph node metastasis.

Central radicality will be categorised into four levels according the extent of lymphadenectomy for central lymph nodes and recorded as described below (Fig. 2):
I.Lymphadenectomy around the origin of the colic artery with complete exposure of the superior mesenteric vein (SMV) and SMAII.Lymphadenectomy around the origin of the colic artery with complete exposure of the SMVIII.Lymphadenectomy around the origin of the colic artery with partial exposure of the SMVIV.Lymphadenectomy around the origin of the colic artery without exposure of the SMV

### Tissue morphometry

By using the photographs of the resected surgical specimens, tissue morphometry will be performed using ImageScope version 10 (Aperio, Vista, CA, USA) [4, 14]. In all cases, the mesentery will be laid out flat without stretching, and the site of the tumour and HVTs will be identifiable. The distance from the tumour and the closest bowel wall to the HVT, the length of the large and small bowel, and the area of mesentery resected will be accurately quantified.

### Macroscopic quality of the mCME specimen

The quality of mCME will be graded based on the Medical Research Council (MRC) CLASICC trial protocol depending on the plane of excision, as described below [4]. Mesocolic grading will be performed by the study committee based on a review of the submitted photographs with blinding of patient outcome. Any discrepancies between the two scores will be discussed before the final grading.
Mesocolic plane (grade A): an intact mesocolonIntramesocolic plane (grade B): significant mesocolic disruptions away from the muscularisMuscularis propria plane (grade C): significant disruptions extending down to the muscularis

### Distribution of metastatic lymph nodes

The location of metastatic lymph nodes will be categorised into three levels based on the Japanese Classification of Colorectal Carcinoma (Fig. 3) [15].
Pericolic lymph nodes: lymph nodes along the marginal arteries and vasa recta of the colon; those on both proximal and distal sides of the primary tumour, which are subcategorised in 5-cm intervals from the edge of the primary tumour.Intermediate lymph nodes: lymph nodes along the colic arteriesCentral lymph nodes: lymph nodes at the origin of each colic artery

### Adjuvant chemotherapy

Adjuvant chemotherapy will be administered based on each patient’s pathologic report and the National Comprehensive Cancer Network guideline [16].

No patient with stage I disease will plan for adjuvant chemotherapy. Patients with stage II–III disease will receive adjuvant chemotherapy using either 5-FU/leucovorin or 5-FU/oxaliplatin/leucovorin (FOLFOX) on a 2-week cycle for 12 cycles, which will be selected based on patient/physician discussions. Adjuvant chemotherapy will be recommended for patients with high-risk stage II tumours, as characterized by poorly differentiated histology (exclusive of cancers that are MSI-H), lymphovascular or perineural invasion, as well as < 12 examined lymph nodes or positive margins. FOLFOX will be recommended for patients with stage III disease, except for those in whom oxaliplatin is contraindicated due to old age, poor performance status, or pre-existing peripheral neuropathy.

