## Methods

### Study design

This is a multi-institutional, prospective, single-arm study. The duration of the study will be approximately 5 years (2 years of inclusion, 3 years of follow-up). Patients will be enrolled at five tertiary colorectal cancer centres in South Korea, including Yonsei Cancer Center, Seoul National University Hospital, St. Vincent’s Hospital, Kyungpook National University Chilgok Hospital, and Korea University Anam Hospital. A complete information leaflet will be provided to the patients during the first consultation, and informed consent will be obtained from them after screening. The preoperative, intraoperative, and postoperative periods will be in complete accordance with the usual care practices of the centres. The baseline demographics and conditions, as well as the perioperative details and the postoperative occurrences, will be recorded on a previously designed case report form. Data from each participating hospital will be collected at the PIONEER database. Data collection forms can be assessed after login on the website. Each hospital has access to their own dataset. The follow-up encompasses 13 postoperative consultations: 1 month, 3 months, and every 3 months thereafter until 36 months.

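### The adjuvant chemotherapy section gives two conflicting rules for stage II patients without high-risk features; they need reconciling into one indication rule for all five centres.

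*Protocol article*

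**What the plan says.** All the relevant text is in the protocol article, mostly under Adjuvant chemotherapy. In order, that section says:

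- General basis: "Adjuvant chemotherapy will be administered based on each patient’s pathologic report and the National Comprehensive Cancer Network guideline".
- Stage I: "No patient with stage I disease will plan for adjuvant chemotherapy".
- Stages II and III together: "Patients with stage II–III disease will receive adjuvant chemotherapy using either" 5-FU/leucovorin or FOLFOX, in 2-week cycles for 12 cycles, "which will be selected based on patient/physician discussions".
- Stage II: "Adjuvant chemotherapy will be recommended for patients with high-risk stage II tumours", followed by the features that define high risk (histology, lymphovascular or perineural invasion, few examined nodes, positive margins).
- Stage III: "FOLFOX will be recommended for patients with stage III disease", except where oxaliplatin is contraindicated.

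Under Study design, the article says that care before, during and after surgery "will be in complete accordance with the usual care practices of the centres". The same section says: "Patients will be enrolled at five tertiary colorectal cancer centres in South Korea".

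**The concern.** The sentence on stages II and III is directive and carries no risk qualifier. The sentence after it recommends treatment for a subset of stage II. If every stage II patient receives chemotherapy, a separate recommendation for the high-risk ones adds nothing. If the recommendation marks who is to be treated, the broader sentence covers too many patients. Both cannot be the rule for a stage II patient without high-risk features.

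Two things are at stake. The first is exposure: whether such a patient is given 12 cycles depends on which sentence is followed. The second is the primary endpoint. Three-year DFS counts recurrence or death from any cause, and adjuvant chemotherapy is a co-treatment that can reasonably be expected to influence it, though the article does not quantify this. The trial has one arm and is judged against a fixed reference of about 80%, so there is no concurrent control in which the same co-treatment would be balanced.

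**Working it through.** **Step 1. The sentences side by side.**

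| Patient group | Stage II–III sentence | Sentence specific to the stage | Consistent? |
|---|---|---|---|
| Stage I | not covered | no adjuvant chemotherapy | yes |
| Stage II, high-risk features | receives | recommended | yes in direction |
| Stage II, no high-risk features | receives | not in the recommended group | **no** |
| Stage III | receives | FOLFOX recommended, with exceptions | yes in direction |

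The conflict is confined to one row. No other section of the article settles it.

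**Step 2. The plan's own figures.** Under Sample size considerations the article gives 80%, 88%, a p-value of 0.025, power 0.90 and the Clopper-Pearson method. Taking 80% as the rate to be exceeded and 88% as the rate to be detected, an exact one-sided binomial test at 0.025 first reaches power 0.90 at n = 225. The rule is at least 192 of 225 disease-free, with actual alpha 0.0245 and power 0.906. Allowing for 10% dropout, 225 / 0.90 = 250. Both stated sizes are reproduced, and nothing here turns on them.

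**Step 3. Illustrative size.** The article gives neither the share of stage II patients without high-risk features nor the effect of chemotherapy on DFS. Assumptions:

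- share of the cohort, s: 20% to 30%, that is 0.20 × 250 = 50 to 0.30 × 250 = 75 patients;
- 3-year event risk without chemotherapy in that group, r: 10% to 15%;
- hazard ratio for chemotherapy: 0.8.

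The shift in overall 3-year DFS between treating none and treating all of the group is s × [r − (1 − (1 − r)^0.8)].

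- Low end: 1 − 0.90^0.8 = 0.0808; 0.20 × (0.1000 − 0.0808) = 0.0038, or 0.38 points.
- High end: 1 − 0.85^0.8 = 0.1219; 0.30 × (0.1500 − 0.1219) = 0.0084, or 0.84 points.

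**Step 4. Scale.** The design difference is 88 − 80 = 8 points. The standard error of a DFS proportion at n = 225 and 88% is √(0.88 × 0.12 / 225) = 0.0217, or 2.17 points. The shift is therefore 0.38 / 2.17 = 0.18 to 0.84 / 2.17 = 0.39 standard errors.

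**Step 5. Effect on the 192-of-225 rule, as an outer bound.** If the 88% presumes that the whole group is treated and none is, power falls from 0.906 to 0.872 (shift 0.38) or 0.822 (shift 0.84). If true DFS is 80% with none of the group treated and all are treated, the chance of passing rises from 0.0245 to 0.034 or 0.048. These are all-versus-none contrasts; a mixture of practices would give less. The article does not say which practice lies behind the 80% or the 88%, so neither direction can be called the likely one.

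**The case against.** The strongest reply is that the section does have a governing rule: its opening sentence ties treatment to the pathology report and one named guideline for every centre. On that reading the guideline decides who is treated, the stage II–III sentence only lists regimens and cycles, and the last two sentences add the stage II indication and the stage III regimen. This reading is coherent, and it gives the list of high-risk features a purpose that the blanket reading takes away. It deserves weight. But it is not what the text says: the sentence says that patients will receive treatment, and nothing limits it to patients already selected. The guideline's content is not in the article, so whether it would resolve the point cannot be checked.

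Two stronger readings are tempting, and the documents support neither.

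- A reader might infer that the five centres will treat these patients differently. No section says so. The usual-care statement is general, and guideline-based care may be the usual care. The choice of regimen is left to discussion with each patient, which is variation by patient and not by centre. Variation between centres is possible, not stated.
- A reader might infer that this wording is why DFS cannot be attributed to the operation or compared with the 80% reference. That limit comes from the single arm and the fixed reference, and it would remain with perfect wording. The adjuvant treatment behind the 80% lies in cited sources not at hand.

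It is also fair to say that larger effects can be produced only by stretching the assumptions. A 40% share with a 5-point benefit gives a 2.0-point shift. At event risks of 10% to 15%, though, a 5-point benefit implies a hazard ratio of about 0.49 to 0.65, and nothing in the article supports that.

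**Conclusion.** The point holds as a contradiction between two stated treatment rules, limited to stage II patients without high-risk features. It is not a complaint about missing detail, so the brevity of a journal article does not excuse it. The textual conflict is certain. Its numerical consequence is small and uncertain: about 0.4 to 0.8 points of overall 3-year DFS, on an assumed share of 20% to 30%, an assumed event risk of 10% to 15% and an assumed hazard ratio of 0.8. The case for acting rests on consistent exposure of patients to chemotherapy and a consistently defined co-treatment behind the primary endpoint, not on the size of the DFS shift.

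**What to change.** The investigators should reconcile the opening sentence, the stage II–III sentence and the high-risk stage II sentence under Adjuvant chemotherapy into one indication rule applied at all five centres. They should also state how that rule relates to the usual-care statement under Study design. If the stage II–III sentence is meant only to list regimens, it should say so. Which indication is right is a clinical matter on which this review takes no position.

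The cost is a wording change. No change to sample size, alpha or endpoint follows from it. How treatment received is recorded and analysed belongs to the case report form and the analysis plan, and is not part of this point.

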### Follow-up

Patients will be scheduled for follow-up every 3 months after surgery until 3 years postoperatively. Complete blood count, blood biochemical examination (aspartate aminotransferase, alanine aminotransferase, creatinine, blood urea nitrogen, blood glucose, and cholesterol), and serum tumour marker (carcinoembryonic antigen) analyses will be performed every 3 months. Further, chest radiography, abdominopelvic computed tomography, and chest computed tomography will be performed every 6 months, and colonoscopy will be performed yearly. All results will be recorded and evaluated by a specialist.

## Discussion

High-quality surgery with the correct surgical plane improves the treatment outcomes for patients with colorectal cancer [4, 14]. Therefore, surgical quality evaluation is essential in clinical studies introducing a new surgical technique or evaluating existing procedures and is one of the key factors for success. Well-designed studies have applied strict qualification criteria for participating surgeons who have completed a learning curve for a specific procedure and make great efforts to investigate the quality of surgery as an objective indicator [4, 17]. However, it is difficult to objectively assess the quality of surgery and there are no common indicators yet.

Several studies have shown the oncological safety and feasibility of laparoscopic colon cancer surgery compared with conventional open surgery [18, 19]. However, prospective studies evaluating the safety and feasibility of laparoscopic CME, Japanese D3 dissection, and mCME in right-sided colon cancer surgery are rare. Furthermore, there are few studies involving quality assessments of right-sided colon cancer surgery using objective measures, and there have not been any definitive clinical studies evaluating surgical quality using intraoperative photographs in laparoscopic right-sided colon cancer surgery.

The PIONEER study is a multi-institutional, prospective, single-arm study evaluating oncologic outcomes after laparoscopic mCME for adenocarcinoma arising from the right side of the colon (defined as from the caecum up to the proximal half of the transverse colon). Remarkably, the study will also evaluate the quality of surgery with objective and rigorous indicators of laparoscopic mCME performed by certified surgeons, which will ultimately demonstrate the significance of surgical quality in treatment outcomes.

Notable previous randomised controlled trials comparing open and laparoscopic colorectal surgery confined the criterion for participating surgeons to performing at least 20 laparoscopic resections [17–19]. However, in this study, only surgeons who performed at least 50 cases of laparoscopic mCME were qualified to participate; therefore, a more stringent criterion was applied here as compared to other previous prospective studies. Moreover, this study adopts a dual-valuation system based on photographs of the surgical field taken during the operation and those of the resected specimens, to maintain the surgical quality and to improve the objectivity of evaluation. For surgeons participating in the PIONEER study, submitting three photographs is mandatory. Photographs to be submitted include a photograph of lymph node dissection and photographs of the front and back sides of the resected surgical specimen for surgical quality control and assurance.

The completeness of mCME will be graded based on the MRC CLASICC trial protocol, by reviewing the photographs of the resected surgical specimen primarily by a pathologist at each centre and finally by central reviewers [4]. The mCME procedure follows the salient concept of the original CME technique (oncologic resection with careful dissection of the mesocolon along the embryologic planes resulting in the complete mobilisation of the mesocolon covered by an intact visceral fascia layer containing all blood vessels, lymphatic vessels, and lymph nodes that may contain disseminated cancer cells) but with a more tailored approach [2, 10]. Therefore, evaluating the smoothness of the fascia covering the resected mesocolon is considered a powerful method for assessing the completeness of mCME, which is a good prognostic factor for colon cancer [4, 14]. However, the weakness of this grading system is that even if the peritoneal-lined mesentery and fascia covering the mesocolon are intact, it does not assess the tumour involvement of the radial margin, which is a risk factor for recurrence [20]. The mCME has different features from the original CME, one of which is securing an adequate radial margin [10]. Consequently, this study is expected to achieve a clearer evaluation of the quality of laparoscopic right-sided colon cancer surgery by overcoming the weakness of the mesocolic grading system.

Precise quantitation of the resected surgical specimen, by measuring the total area of the resected mesocolon and the distance from the muscularis propria to the nearest mesenteric and radial margin, is an indicator of surgical and oncological quality, as well as the measuring plane of surgery and lymph node retrieval [14]. However, considering the surgical principle that central ligation of main supplying vessels reduces the risk of residual metastatic lymph nodes and enables accurate staging, it is very challenging to assess the extent of lymph node dissection and CVL by using tissue morphometry and the number of retrieved lymph nodes. To assess the central radicality of laparoscopic mCME, the surgical field after lymph node dissection and specimen removal will be reviewed primarily by the attending surgeon at each centre and finally by central reviewers based on the photographs obtained during the procedure.

To our knowledge, this study will be the first prospective trial to assess the oncologic safety of laparoscopic mCME for right-sided colon cancer, supported by the thorough surgical quality control system of the study group. Patient-tailored surgical treatment for right-sided colon cancer can be developed based on the present study results, including the determination of the optimal extent of dissection and the extent of the lymphadenectomy. Additionally, it may aid in the development of a global standardised surgical procedure for right-sided colon cancer.

## Data Availability

Not applicable in this study protocol. After finishing the enrollments of the participants, the raw datasets are available from the corresponding author on reasonable request.

## Abbreviations

CVL: central vascular ligation
CME: complete mesocolic excision
DFS: disease-free survival
HVTs: high vascular ties
MRC: Medical Research Council
mCME: modified CME
SMA: superior mesenteric artery
SMV: superior mesenteric vein
